# 1 INTRODUCTION

## 1.1 BACKGROUND

Menstrual bleeding complaints affect quality of life and comprise a substantial societal burden, including major impact on health care use and costs. In the UK, 1 million women annually seek help for heavy menstrual bleeding (HMB; Clinical Guideline 44; <http://www.nice.org.uk/guidance/cg44>) and reported treatment costs exceed £65m; an estimated 3.5 million work-days are lost annually (7).

Current commonly prescribed medical treatments for HMB include COX-inhibitors, anti-fibrinolytic therapy, and the levonorgestrel-releasing intra-uterine system (LNG-IUS). NICE recommends LNG-IUS as the first line medical treatment. The LNG-IUS significantly reduces the burden of heavy menstrual bleed compared to non-hormonal treatments, substantially reduces menstrual blood loss, often resulting in amenorrhoea, but the unpredictable unscheduled bleeding may be problematic, with up to a third ceasing use within 2 years (8, 9).

A new group of pharmacological agents, called selective progesterone receptor modulators (SPRMs) are in development and have the potential to provide effective oral treatment for HMB. These SPRMs impart a tissue-specific partial progesterone antagonist effect, acting on progesterone receptors in both endometrial and underlying myometrial tissue. Ulipristal Acetate (UPA) is the only SPRM to have been licensed for use in clinical practice albeit restricted to two cycles of 3 month pre-treatment of fibroids prior to surgical removal. The introduction of this drug followed evaluation in two concurrent randomised controlled trials (RCTs) (10); 'PEARL I' assessed the efficacy of UPA 5mg and 10 mg daily on uterine bleeding and fibroid volume against placebo and 'PEARL II' assessed the efficacy and side effects of UPA versus the gonadotrophin-releasing hormone analogue (GnRHa) leuprolide acetate for treating symptomatic uterine fibroids prior to surgery (10). Both trials demonstrated control of HMB in over 90% of women and amenorrhoea in over 70% women. Control of HMB was achieved significantly more quickly in the UPA group. There was a statistically significant reduction in uterine fibroid size (-21% in the 5mg and -12% in the 10mg groups). Compliance with treatment over 3 months was high in both studies (96% and 98%) and reported side-effects were limited to minor complaints, of which headache (4%) and breast complaints (4%) were the most common, with no difference between active drug and placebo.

Different classes of SPRM induce distinct endometrial morphology, which can be confused with complex hyperplasia. To date detailed analysis of endometrial histology has been limited to treatment with UPA for 3 months (11, 12); detailed histological evaluation showed altered architectural glandular features including extensive cystic dilatation. The glandular epithelium appeared inactive or contained abortive subnuclear vacuolization, occasional mitoses, and apoptosis. Histology returned to normal after discontinuation of treatment (12). Treatment of monkeys for 39 weeks revealed similar endometrial histology to that in women (13).

PTEN is a tumour suppressor gene product, described as a gatekeeper for initiation of carcinogenesis in the endometrium (14, 15). Loss of PTEN function occurs as an early event in endometrial carcinogenesis and has been proposed as a biomarker for premalignant disease even in histologically normal endometrium (14, 16). Progesterone plays an important role in eliminating PTEN-deficient endometrial cells when administered via a progestin-releasing intrauterine device (17) or systemically (18). A compound with progesterone antagonist activity, such as UPA, may raise concerns of an unfavourable effect on PTEN expression and thus on the potential to influence predisposition to latent endometrial precancerous lesions. Hence study of PTEN in women administered UPA is important.

## **1.3 RATIONALE FOR STUDY**

The rationale for using UPA to control HMB is because HMB is a clinical area of unmet need, with a community prevalence of 25%, and can significantly impact on women's lives and burden individuals and healthcare systems. HMB often co-exists with uterine fibroids, benign tumours of uterine muscle present in up to 80% of women of reproductive age. Medical therapy for HMB, particularly when fibroids are present, may be either ineffective or associated with unacceptable side effects. Preservation of fertility is an issue for many women, given the trend for later births.

It is clear that there is an urgent need to develop safe, simple, acceptable, fertility-sparing medical treatments for HMB. SPRMs may provide a solution in light of the mounting evidence that progesterone and the progesterone receptor play a pivotal role in both menstruation and fibroid growth and development. The PEARL studies demonstrated control of HMB in over 90% of women and amenorrhoea in over 70% women. There were no serious side effects or complications associated with UPA; adverse events were limited to minor complaints. However despite profound therapeutic potential, robust data on long term effectiveness and the mechanisms of action of SPRMs in women with HMB remain to be elucidated. There is an urgent need to evaluate the use of UPA against current best medical treatment for all women with HMB.

## **2 STUDY OBJECTIVES**

### **2.1 RCT OBJECTIVES**

#### **2.1.1 Primary Objective**

- Determine if UPA is more effective at reducing the burden of HMB symptoms than LNG-IUS after 12 months of treatment.

#### **2.1.2 Secondary Objectives**

- Ascertain whether UPA use beyond 3 months and up to 12 months duration is associated with histological changes to the endometrium, and if so, whether this compromises safety.

- Ascertain whether UPA is more effective than LNG-IUS in relation to menstrual blood loss, sexual activity, generic quality of life, satisfaction with treatment, patient reported adverse events, and compliance at 3, 6 and 12 months.
- Determine the response to UPA and LNG-IUS treatment difference in the presence of uterine fibroids in terms of (i) alleviation of HMB and (ii) change in uterine/fibroid volume.

### **2.1.3 Mechanistic Sub-study Objectives**

To understand how UPA causes a reduction in menstrual bleeding and uterine/ fibroid volume in women with HMB, we will determine whether:

- Administration of UPA alters endometrial cell function (proliferation, apoptosis, expression of steroid receptors, tumour suppressors or inflammatory mediators).
- UPA reduces blood flow and blood volume in the endometrium, junctional zone, outer myometrium and fibroid tissue.
- UPA alters the volume fraction of the extracellular matrix in the above tissues.
- UPA reduces uterine and fibroid volume.

## **2.2 RCT OUTCOMES**

### **2.2.1 Primary outcome**

The primary outcome measure is the condition-specific Menorrhagia Multi-Attribute Scale (MMAS) designed and validated to capture the impact of HMB on women's day-to-day life (19). HMB is a subjective problem and quality of life is affected by practical difficulties and the impact on social life, psychological wellbeing, physical health, work routine and family life. The menorrhagia multi-attribute utility assessment (MMAS) questionnaire attempts to capture the consequences of HMB on these domains with 6 questions each with 4 levels of response. Summary scores range from 0 (not affected) to 100 (worst affected). The primary time point for analysis will be at 12 months.

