## **9 STATISTICS AND DATA ANALYSIS**

### **9.1 SAMPLE SIZE CALCULATION**

#### **9.1.1 RCT**

The trial has been designed to be able to detect a clinically useful difference in MMAS score between the two groups at twelve months with high power. The ECLIPSE Trial, which evaluated the effectiveness of LNG-IUS against Standard treatment for HMB (21) using MMAS as the primary outcome, demonstrated a difference of 13 points between the groups with a standard deviation of 24 points. This difference considered to be clinically meaningful (22) and is equivalent to approximately 0.5 standard deviations. To detect a difference of this size with 90% power ( $p=0.05$ ) would require 86 women in each group (172 in total). To allow for a 20% loss to follow-up or pregnancy, the sample size has been inflated to 220 women in total.

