### **9.2.1 Primary analysis**

A linear regression model will be used to estimate differences in MMAS responses between the two groups at each time point. Baseline score and the minimisation variables (listed in section 5.5.1) will be included in the model as covariates. The statistical significance of the treatment group variable will be determined by an associated chi-squared test.

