### **9.2.4 Handling missing data and other sensitivity analysis**

Every attempt will be used to collect full follow-up data on all women. In particular, the trial team will endeavour to follow-up participants even after protocol treatment violation. It is thus anticipated that missing data will be minimal. Patients with missing primary outcome data will not be included in the primary analysis. This presents a risk of bias. Thus, secondary sensitivity analyses will be performed to investigate the impact of any missing data for the primary, as well as any important secondary outcome. This will include worst (for those randomly missing) and best case assumptions (for those not able to complete the primary outcome as they no longer can have menstrual bleeding, i.e. because they have had a hysterectomy). We will also simulate missing responses using a multiple imputation approach. To explore the sensitivity of the primary MMAS

analysis to any ceiling effects (i.e. a high proportion returning a maximum responses, i.e. no problems with bleeding), a Tobit regression model will also be implemented.

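### The protocol gives two opposite directions for the primary MMAS score, so the ceiling Tobit analysis in section 9.2.4 does not fit the scale defined in section 2.2.1

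*Protocol*

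**What the plan says.** Section 2.2.1 of the protocol defines the primary outcome, the MMAS summary score, at 12 months: "Summary scores range from 0 (not affected) to 100 (worst affected"). The Trial Summary repeats this definition. On it, lower is better.

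Section 9.2.4, on sensitivity analyses of the same outcome, plans for "any ceiling effects (i.e. a high proportion returning a maximum responses, i.e. no problems with bleeding), a Tobit regression model will also be implemented". Here the top of the scale is the good end, so higher is better. The same section says of missing data: "This will include worst (for those randomly missing) and best case assumptions". The best case is meant for women who can no longer menstruate, for example after hysterectomy. No numerical score is given for either case.

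The other places that mention the MMAS do not state a direction:

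- The primary objective (2.1.1): "Determine if UPA is more effective at reducing the burden of HMB symptoms than LNG-IUS after 12 months of treatment".
- The primary model (9.2.1): "A linear regression model will be used to estimate differences in MMAS responses between the two groups at each time point".
- The sample size basis (9.1.1), an earlier trial that "demonstrated a difference of 13 points between the groups with a standard deviation of 24 points".

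**The concern.** This is the primary endpoint, and an analyst needs the direction of its scale for three things:

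- which sign of the UPA minus LNG-IUS difference is a benefit;
- which end of the scale the Tobit model treats as censored;
- which number stands for the best case and which for the worst case.

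With two opposite definitions, each of these depends on which section is read. The Tobit model is the most exposed, because section 9.2.4 describes it in terms that fit only a higher-is-better scale. If the 2.2.1 scale is the true one and the model is built as a ceiling model, it censors the wrong women. Agreement between its result and the main analysis would then be false reassurance. The reading of the primary result also matters before the final report, because section 11.4 sends interim analyses of this outcome to the data monitoring committee.

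**Working it through.** **1. The two statements side by side**

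| | Trial Summary and 2.2.1 | 9.2.4 |
|---|---|---|
| No problems with bleeding | 0 | maximum |
| Worst affected | 100 | by implication, minimum |
| Better direction | lower | higher |
| Pile-up of women without problems | floor at 0 | ceiling at 100 |
| UPA minus LNG-IUS if UPA is better | negative | positive |
| Best case / worst case | 0 / 100 | 100 / 0 |

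The first four rows follow directly from the text. The last two follow from the direction and are not written in the protocol. Within 9.2.4, the words for ceiling and maximum support each other, so it reads as a reversed scale rather than one mistyped word.

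**2. What does not depend on direction**

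Inputs from 9.1.1 are a difference of 13, SD 24, an effect "equivalent to approximately 0.5 standard deviations", 90% power and p = 0.05, with 86 women per group. Section 9.2 specifies two-sided tests.

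- At 0.5 SD, a two-sample t-test needs 85.03 per group, which rounds up to 86. The protocol's figure is reproduced.
- With 20% loss, 172 / 0.80 = 215. The protocol rounds up to 220.
- With 86 per group and SD 24, power is 90.6% for +12 or -12 points and 94.4% for +13 or -13.

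Reversing the scale (score becomes 100 minus score) changes the sign of the linear-regression estimate. It does not change its absolute size or its two-sided p-value.

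**3. A Tobit limit at the wrong end**

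The protocol gives no distribution of scores, so this is an illustration under assumed values: 20,000 simulated women, half in each arm; normal latent scores on a higher-is-better scale with means 80 and 93; SD 24; a true benefit of 13; scores clipped to 0–100; no covariates. About 20% and 38% of the arms sit at the no-problem end, and 0.03% of all women sit at the worst end.

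| Scoring | Linear model | Tobit, upper limit 100 | Tobit, lower limit 0 |
|---|---|---|---|
| Maximum = no problems | +9.3 | +13.0 | +9.3 |
| 0 = not affected (2.2.1) | -9.3 | -9.3 | -13.0 |

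With the limit at the no-problem end, the model recovers the assumed 13 points. With the limit at the other end, it returns the linear estimate unchanged. How large the gap is depends on the assumed pile-up. That the wrong end gives essentially no correction depends only on few women scoring at the worst end.

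**4. A best- or worst-case score at the wrong end**

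Women analysed per arm: (220 / 2) × 0.80 = 88. A woman scored 100 instead of 0, or the reverse, moves her arm's mean by 100 / 88 = 1.14 points. The protocol gives no count of such women, so a range is assumed, with all of them in one arm:

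- 1 woman: 1.1 points
- 3 women: 300 / 88 = 3.4 points
- 5 women: 500 / 88 = 5.7 points, which is 5.7 / 13 = 44% of the target difference

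**The case against.** The strongest reply is that section 9.2.4 fixes no number. It names no Tobit limit and no best- or worst-case score, and it describes the pile-up by its meaning, the absence of bleeding problems. Its best case is likewise a clinical state that stays the same whichever number represents it. An analyst who follows the meaning will censor and score at the correct end. This stands as far as it goes: a model censored at the wrong end is a risk created by the wording, not a limit the protocol specifies. But ceiling and maximum are also in the text, and on the 2.2.1 scale they point to the wrong end.

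A second reply is that sign conventions, Tobit limits and imputation values usually belong in the statistical analysis plan, which section 9.2 promises before any analysis. That is right, and their absence from the protocol is not the complaint. The complaint is that the protocol makes two incompatible statements, and a later plan inherits whichever one its author reads.

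A reader might also infer that the primary effect itself is reversed, so that a 13-point benefit could be reported as a 13-point harm, a swing of 26 points. The documents do not support that. The protocol states no sign, and the instrument's own scoring fixes the data. The MMAS is also collected at baseline, in women enrolled because they find their bleeding heavy. Read backwards, those women would appear little affected at entry, which should expose the error. The swing describes a misreading, not a bias in the estimate.

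**Conclusion.** The contradiction is real and concerns the primary endpoint. The Trial Summary and section 2.2.1 make 0 the good end, section 9.2.4 makes the maximum the good end, and the protocol alone does not show which is right.

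The direct operational effect falls on the sensitivity analyses in 9.2.4. On the 2.2.1 scale, a ceiling Tobit model does not do its job: in the illustration it leaves 9.3 points where the correct limit gives 13.0. Best- and worst-case scores at the wrong end would move an arm mean by about 1.1 points per woman. Both figures rest on assumed values, for the score distribution and for the number of women concerned. The other effect is on how the sign of the primary result is read.

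It would go too far to say that the primary analysis is invalid or that the protocol assigns wrong scores. Sample size, power, the two-sided p-value and the absolute size of the linear-regression estimate are the same under either direction.

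**What to change.** Confirm the direction of the MMAS from the instrument's scoring rules and correct whichever text is wrong, so that the Trial Summary, section 2.2.1 and section 9.2.4 agree.

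- If 0 is not affected, 9.2.4 should speak of a floor effect with the Tobit limit at 0, the best case at 0 and the worst case at 100.
- If the maximum means no problems, the Trial Summary and 2.2.1 should be reversed. The limit and the best case are then 100, and the worst case is 0.

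Either way, tie the Tobit limit and the best/worst-case scores to the numerical values of the two ends of the agreed scale. The sign of the UPA minus LNG-IUS difference that favours UPA then follows and can be carried into the statistical analysis plan.

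The cost is a few words in one to three places. It needs no new data, no change in sample size and nothing from participants.

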### **2.2.2 Secondary outcomes**

- Menstrual bleeding will be captured by validated Pictorial Blood Loss Assessment Chart (PBAC) (20). The standard PBAC is a validated and well used assessment of menstrual blood loss in women. It will be used to generate the incidence of amenorrhoea, light, normal and heavy menstrual bleeding. It will also be used to ascertain the number of days bleeding per month.
- Cycle regularity and duration.
- Visual analogue scales (0-10) for pelvic pain during periods, intercourse and at other times
- Uterine Fibroid Symptom and Quality of Life (UFS-QoL) instrument, which contains a health related quality of life (HRQoL) domain and a symptom domain (21). Sexual Activity Questionnaire (22), a measure of sexual functioning, used in other HMB trials (9). The sexual activity questionnaire is a valid, reliable and acceptable measure for describing the sexual functioning of women in terms of pleasure and discomfort. It is quick and easy to administer and has good face validity delineating between the sexual functioning of pre and post-menopausal women.

- General quality of life questionnaires - EuroQoL-5D (EQ-5D-5L) (23) and ICECAP-A (24).
- Satisfaction with treatment outcome measured on a 5-point Likert scale.
- Participant rating of effect of treatment on HMB over 12 months measured on a 4-point Likert scale.
- Whether participant is willing to recommend the treatment to a friend.
- Surgical intervention (hysterectomy, endometrial ablation and other gynaecological surgery)
- Adherence to trial treatments and reasons for changing treatment, as reported by the participant.
- Serious adverse events and reactions reported by participants, principally those that are serious and detailed in the respective Summary of Product Characteristics (SmPC) and those that are unexpected.
- Clinical measurements via pelvic ultrasound: uterine volume, evidence of adenomyosis, presence of fibroids, largest fibroid volume, endometrial thickness, endometrial appearance (regular/irregular), evidence of ovarian cysts.
- Clinical measurement via endometrial biopsy: primary diagnosis (normal/benign/hyperplasia/malignant) and further sub-diagnoses if non-normal.
- Clinical measurement via blood samples: serum haemoglobin and oestradiol levels.

## 2.3 FUNCTIONAL AND MECHANISTIC OUTCOMES

- Impact on endometrial tissue architecture including regulation of the vascular compartment
- Impact on endometrial steroid responsiveness, proliferation, survival and inflammatory processes
- Expression of genes implicated in pre-malignant change including tumour suppressors
- Effects on uterine/ fibroid structure and vascularity as determined by MRI-DCE and high resolution structural MRI

## 3 STUDY DESIGN

### 3.1 DESIGN

A multicentre, randomised controlled trial of UPA compared to LNG-IUS with a concurrent mechanistic evaluation of UPA. A trial schema is shown in Appendix 2.

## 4 STUDY POPULATION

The target population is women who present to primary and secondary care with HMB. Participants will be recruited from the gynaecological, out-patient clinics of participating centres, fitting around their current service provision. Recruitment will be supported by dedicated research nurses, who will work with local gynaecology leads. A flowchart of the recruitment process is shown in Figure 1.

## **4.1 NUMBER OF PARTICIPANTS**

UCON will aim to recruit a minimum of 220 women into the randomised controlled trial and from those, approximately 20 women will be required to undergo more detailed evaluation to contribute to the mechanistic study which is conducted at the Royal Infirmary of Edinburgh. The statistical basis of the sample size calculation is detailed in Section 9.1.

Recruitment will take place over 24 months from 5 centres (i.e. 2 participants/ centre/month).

## **4.2 ELIGIBILITY**

In order to be randomised into the UCON trial, all eligibility criteria must be satisfied. Investigators will be asked to confirm each eligibility criteria at randomisation.

### **4.2.1 Inclusion Criteria**

- Aged 18 years or over
- Menstrual bleeding that she perceives to be heavy and troublesome
- Willing to receive medical treatment with either UPA or LNG-IUS
- Willing to undergo two pelvic ultrasounds
- If allocated to UPA, willing and eligible to undergo two endometrial biopsies with the possibility of a third and fourth (i.e. up to four biopsies)
- If allocated to UPA mechanistic sub-study, willing and eligible to undergo three endometrial biopsies with the possibility of a fourth and fifth (i.e. up to five biopsies). If 'No' may be randomised to RCT if UPA endometrial biopsy consent given
- Willing to use barrier contraception if allocated to UPA
- Given written informed consent
- Willing and eligible to undergo up to three magnetic resonance imaging scans? If allocated to UPA, mechanistic sub-study only. If 'No' may still be randomised to RCT

### **4.2.2 Exclusion Criteria**

- Post-menopausal
- A >14 week fibroid uterus and/or cavity length >11 cm confirmed by ultrasound scan
- Submucosal fibroids >2cm diameter confirmed by ultrasound scan
- Contraindications to UPA or LNG-IUS
- Intention to continue current use of Cytochrome P450 (CYP3A4) inhibitors
- Intention to continue current use of Cytochrome P450 (CYP3A4) inducers (e.g. Phenytoin, carbamazepine, rifampicin, St John's Wort)

- Intention to continue current use of P-glycoprotein substrates (e.g. digoxin)
- A past, current or suspected diagnosis of endometrial hyperplasia or neoplasia
- Severe hepatic impairment
- Epilepsy managed with carbamazepine, phenytoin
- Significant renal impairment
- Pregnant
- Current plans to become pregnant within 12 months
- Currently breastfeeding
- Severe asthma that is not sufficiently controlled by oral glucocorticoids
- Past or current known history of with uterine, cervical, ovarian or breast cancer.
- Current use of progestagen-releasing intrauterine device (except if allocated within UCON)
- Intention to continue regular use of Mefenamic acid
- Intention to continue regular use of Tranexamic acid
- Intention to continue regular use of GnRH analogues
- Intention to continue regular use of Progestagen-only contraceptive
- Intention to continue regular use of any combined oral contraceptive pills
- Intention to continue regular use of hormonal replacement therapy

